### Inclusion criteria

The inclusion criteria consisted of 1) Iranian nationality, 2) residency in Tabriz, 3) literacy, 4) infant age range within 28–37 weeks, 5) passage of 4–6 months after the preterm birth of the infant, 6) lack of disease and malformations of the infants, 7) no history of stressors in the last 6 months (e.g., divorce, death of a family member, and diagnosis of a family member with an incurable or life-threatening disease), 8) breastfeeding (exclusively or with auxiliary milk).

### Exclusion criteria

The exclusion criteria were failure to complete the questionnaire completely and unwillingness to continue the study.

### Scales and data collection

Quantitative data will be collected using 5 questioners, including:

**Sociodemographic characteristics questionnaire:** consisted of questions about the mother’s and father’s ages, the mother and father’s education, number of pregnancies, number of deliveries, pregnancy interval, gestational age at delivery, and the infant’s age and sex.**Socioeconomic Status Questionnaire:** This questionnaire had 19 questions about occupational status, level of education of the couple, residence, status of home ownership, the amount of rent or mortgage, house area, family economic status (evaluating eight items), family size, number of family members, ethnicity, insurance, receiving food aid, whether being supported by social organizations, monthly income, and total family expenditure. The economic status will be assessed as poor, average, and good by having less than 3 items, 4 to 6 items, and more than 7 items, respectively. The validity of the researcher-made socioeconomic questionnaire have been evaluated in Dolatian et al. study through content validity, and its reliability have been assessed using internal consistency, Cronbach’s alpha (0.876), and retest (0.916) [23].**Multiple Scale of Perceived Social Support Questionnaire (MSPS):** This is a social support questionnaire designed by Zimet et al. that encompasses 12 items scored based on a Likert scale. The questionnaire evaluates three domains of perceived support from the family (four items), perceived support from family members and acquaintances (four items), as well as perceived support from friends (four items). The items are scored based on a seven-point Likert scale from “completely disagree” (score: 1) to “completely agree” (degree: 7) in which the minimum and maximum scores are 12 and 84, respectively [19]. Total scores of answering the questions fall in three categories: Low (scores 12–48), Moderate (scores 49–68) and high (scores 69–84) social supports [24]. This instrument also has been validated in Iran by Bagherian-Sararoudi R et al., as Cronbach’s coefficient has been found to be 0.92 for the scale and 0.89, 0.92 and 0.87, for friends, significant others and family subscales, respectively [25].**The Depression, Anxiety and Stress Scale (DASS-21):** This is a 21-item questionnaire first presented by Love bound in 1995 that uses 7 questions to measure each of the symptoms of stress, anxiety, and depression. This questionnaire was designed as a Likert questionnaire. The lowest score for each question was a score of zero and the highest the score of 3. In each section related to anxiety, depression and stress, a score of 1–7 indicated a mild level, a score of 8–14 indicated a moderate level, and a score of 15–21 indicated a severe level of anxiety, depression and stress. This questionnaire has been used in various surveys and its validity and reliability have been confirmed [23].**The breastfeeding self-efficacy questionnaire**: It was designed by Dennis (2003). This questionnaire is a 33-item scale and is scored by a 5-point Likert scale from always confident (5) to not at all confident (1). Scores range from 33 to 165, with 33–76 considered low self-efficacy, 77–120 average self-efficacy, and 121–165 regarded as high self-efficacy. The reliability of this questionnaire was reported 82% in a study by Varaei et al. [26].

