### Objectives of the second phase: quantitative study

To determine Socio-economic situation among mothers of premature infants.To determine perceived social support among mothers of premature infants.To determine Psychological factors among mothers of premature infants.To determine breastfeeding self-efficacy in mothers of premature infants.To determine the association between Socio-economic situation with breastfeeding self-efficacy.To determine the association between perceived social support with breastfeeding self-efficacy.To determine the association between Psychological factors with breastfeeding self-efficacy.

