
### Data analysis

The quantitative data will be analyzed with SPSS-22. Sociodemographic, MMAS-8, DASS-21, self-efficacy breastfeeding questionnaires score will be described by frequency (percent), as well as mean (standard deviation) if the data are normally distributed. The relation between Sociodemographic, MMAS-8, DASS-21 with self-efficacy breastfeeding will be determined using the independent test, ANOVA and Pearson correlation tests in the bivariate analysis, and logistic linear regression adjusting the confounding variables in the multivariate analysis. Then, the univariate logistic regression will be used to control confounding variables.

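### As written, economic counts of 3 and 7 have no class, and the DASS-21 bands give no level for a score of 0

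*Protocol article*

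**What the plan says.** Both rules are in the protocol article under Scales and data collection.

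- **Economic status.** The socioeconomic questionnaire has 19 questions. One element is "family economic status (evaluating eight items"). The result is graded poor, average or good "by having less than 3 items, 4 to 6 items, and more than 7 items", in that order.
- **DASS-21.** The instrument "uses 7 questions to measure each of the symptoms of stress, anxiety, and depression". For the items, "The lowest score for each question was a score of zero and the highest the score of 3". On each subscale, "a score of 1–7 indicated a mild level, a score of 8–14 indicated a moderate level". The top band, severe, covers 15 to 21. No normal or symptom-free level is named.

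The objectives of the second phase include "To determine Psychological factors among mothers of premature infants", a matching objective for socio-economic situation, and the association of each with breastfeeding self-efficacy. Under Data analysis for that phase, questionnaire scores, DASS-21 among them, "will be described by frequency (percent), as well as mean (standard deviation) if the data are normally distributed". Bivariate relations use the independent test, ANOVA and Pearson correlation, followed by regression.

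**The concern.** A banding rule should send every possible score to exactly one class. Neither of these does.

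For economic status, the gaps lie at both class boundaries. Two analysts working from the same text could code counts of 3 and 7 differently, and each choice changes who counts as poor, average or good. The exclusion criteria do not settle it: they remove incomplete questionnaires and unwilling participants, while a mother with 3 or 7 items has complete data.

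For DASS-21, the problem is what the lowest band means. With mild starting at 1, the descriptive table has no row for mothers without symptoms, and the smallest possible non-zero answer is reported as a mild level of depression, anxiety or stress. The third phase hands the quantitative results to an expert panel that will write strategies, so such a table could be misread there.

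**Working it through.** No sample-size or power formula applies, and the plan gives no figure to reproduce. The check is to list every possible score and apply the bands as written.

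**Economic status.** Input: eight items, so counts run from 0 to 8 (nine values).

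| Count | Class as written |
|---|---|
| 0, 1, 2 | poor |
| 3 | none |
| 4, 5, 6 | average |
| 7 | none |
| 8 | good |

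Two of nine counts have no class, and *good* requires all eight items. If the outer bounds are read as inclusive (0–3, 4–6, 7–8), all nine counts are covered.

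**DASS-21 subscale.** Inputs: seven items, each scored 0 to 3. Minimum 7 × 0 = 0; maximum 7 × 3 = 21; 22 possible scores.

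- 1–7 mild, 8–14 moderate, 15–21 severe: 21 scores covered.
- 0: no level.
- Smallest non-zero score: one item rated 1 and six rated 0, total 1, recorded as mild.

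Inclusive wording does not repair this one. If 0 were folded into mild, there would still be no symptom-free class.

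**Comparison with the other banded scales in the same section.**

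- Perceived social support: 12 items scored 1–7, range 12–84; bands 12–48, 49–68, 69–84. No gap.
- Breastfeeding self-efficacy: 33 items scored 1–5, range 33–165; bands 33–76, 77–120, 121–165. No gap.

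**Illustration of how many mothers the economic gap could touch.** The document gives no distribution of the count. Assume, for scale only, that the eight items are independent with a common ownership probability p. The unclassified share is P(3) + P(7) = C(8,3)p³(1−p)⁵ + C(8,7)p⁷(1−p).

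| p (assumed) | P(3) | P(7) | Sum | Of 360 mothers |
|---|---|---|---|---|
| 0.5 | 0.219 | 0.031 | 0.250 | 90 |
| 0.6 | 0.124 | 0.090 | 0.213 | 77 |
| 0.7 | 0.047 | 0.198 | 0.244 | 88 |

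Real household items are unlikely to be independent, so these figures show only that the gap need not be rare.

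**The case against.** The strongest reply is that the economic gap is loose wording. With a middle band of 4 to 6, the outer bands most naturally mean up to 3 and 7 or above, and on that reading nobody is unclassified. That is probably right, but the article does not say so and no other section corrects it. The economic class is also only one element of a 19-question instrument that covers occupation, education, housing, income and more, so the gap does not undermine the whole socioeconomic exposure. That stands.

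For DASS-21, a score of 0 can be read as no symptoms, and the bands can be seen as plain descriptive thirds of 1 to 21. Raw scores need no bands for the planned means, Pearson correlation or regression. That also stands, and it limits the point to categorical uses.

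A reader might go further and infer three things that the document does not support:

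- *Nearly every mother will be counted as a case.* The article does not use the bands to define cases and gives no item response rates. The planning mean of 8.3 and SD of 4.6 (Sample size and sampling method) are attributed to psychological factors and depression in a cited study, with no instrument named, so they cannot be applied to a 0–21 subscale.
- *The reference group is lost.* ANOVA and regression do not need a symptom-free group; mild could serve as reference.
- *The mild band of 1–7 departs from the instrument's published cut-offs.* Those cut-offs are not in the document, so this cannot be judged here.

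**Conclusion.** The point holds as a defect in two stated scoring rules. Economic counts of 3 and 7, two of nine, have no class, and *good* means all eight items. A DASS-21 subscale score of 0, one of 22, has no level, no symptom-free class exists, and any score of 1 or more is at least mild. This follows from the text alone.

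The reach is limited to the frequency tables and to any comparison that uses these categories (independent test, ANOVA). The Data analysis section does not name the socioeconomic questionnaire separately; I assume that its economic class would be handled by the same methods, since the objectives call for its description and its association with self-efficacy. Analyses of raw DASS-21 scores are not affected. The 21–25% range for unclassified mothers is illustrative and rests on independent items with 50–70% ownership. These are explicit cut-offs, not details left to a fuller document, so they should be corrected, but they do not threaten the study as a whole.

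**What to change.** Three changes to the scoring and analysis text:

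1. Make the economic classes exhaustive: 0–3 poor, 4–6 average, 7–8 good, or the boundaries of the source questionnaire if they differ.
2. Give each DASS-21 subscale a class that contains 0, with all cut-offs taken from the instrument's own source and cited to it.
3. State that the association models use the three continuous DASS-21 subscale scores and that the bands serve description only. This fits the correlation and regression already planned.

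The cost is a few lines of wording. The questionnaires, sampling and data collection stay as they are. The rules should be fixed before the scores are classified, so that the handling of boundary scores is not chosen after seeing the data.

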
### Data analysis

The quantitative data will be analyzed with SPSS-22. Sociodemographic, MMAS-8, DASS-21, self-efficacy breastfeeding questionnaires score will be described by frequency (percent), as well as mean (standard deviation) if the data are normally distributed. The relation between Sociodemographic, MMAS-8, DASS-21 with self-efficacy breastfeeding will be determined using the independent test, ANOVA and Pearson correlation tests in the bivariate analysis, and logistic linear regression adjusting the confounding variables in the multivariate analysis. Then, the univariate logistic regression will be used to control confounding variables.

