### Sample size and sampling method

Based on a study conducted by Nego et al. [8], and a confidence coefficient of 95%, statistical power of 90%, standard error of the mean (SEM) of 0.05, mean values of 141.1, 69.3, and 8.3, and the highest standard deviations of 15.9, 9, and 4.6 regarding the breastfeeding self-efficacy scale, perceived social support, and psychological factors and depression the necessary sample sizes were calculated at 20, 26, and 240 subjects, respectively. Since the sample size based on psychological factors and depression was larger, it was selected as the sample size of the study. Regarding the cluster sampling method and a design effect of 1.5, the final sample size was estimated at 360 participants.

Sampling will be conducted in the healthcare centers in Tabriz. There are 82 public healthcare centers (*n* = 40) and posts (*n* = 42) in different regions of the city that provide primary care services, including postpartum care and infant care, free of charge. All the mothers and infants in Tabriz have health records in these healthcare centers and posts. A two-stage cluster sampling will be carried out so that 13 healthcare centers and 14 healthcare posts were selected using a randomizer software (www.random.org). A list of all breastfeeding mothers of premature infants at each center will be extracted from the health records and the samples will be randomly selected from the ordered numbers. Afterward, Using the phone number registered in each record, the researcher will call the potential participants and invite them to participate in the study. The eligible participants will be provided with full explanations about the study objectives and procedures. Also, informed consent will be obtained before collecting information, and be emphasized the importance of honest answers to the questionnaire, and asked them to complete the anonymous questionnaires in a private room. A number of participants are likely to be illiterate, so the questionnaires will be completed by the researcher in order for the data collection method to be the same for all individuals.

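### The phase-two sample is drawn and enlarged for clustering (27 centres and posts, design effect 1.5), but the named tests treat the mothers as independent

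*Protocol article*

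**What the plan says.** Under Sample size and sampling method (second phase), the protocol article states: "A two-stage cluster sampling will be carried out so that 13 healthcare centers and 14 healthcare posts were selected". Within each selected unit a list of eligible mothers is taken from the health records, and "the samples will be randomly selected from the ordered numbers". The section gives base sizes for three scales ("the necessary sample sizes were calculated at 20, 26, and 240 subjects, respectively") and takes the largest, which was derived for psychological factors and depression. It then inflates that figure: "Regarding the cluster sampling method and a design effect of 1.5, the final sample size was estimated at 360 participants".

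Under Data analysis for the same phase, the scales are to be described by frequency and percent, or by mean and standard deviation. The relations with self-efficacy "will be determined using the independent test, ANOVA and Pearson correlation tests in the bivariate analysis". A multivariable regression and a univariate logistic regression follow. The only adjustment named is for confounding variables. The article mentions no random effect for centre, no cluster-robust standard errors, no survey procedure and no weights.

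**The concern.** By adopting a design effect of 1.5, the plan says that mothers from the same centre or post resemble each other enough to raise the variance of a mean by half. A larger sample restores the precision lost to clustering. It does not correct a standard error computed by a method that ignores clustering.

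The t-test, ANOVA, Pearson correlation and regression in their standard forms take 360 as the number of independent observations. On the plan's own premise the equivalent number for a mean is 360 / 1.5 = 240. Where both exposure and outcome cluster by centre, p-values come out too small and intervals too narrow. The quantitative results go to the expert panel that develops the strategies in phase three, so overstated associations could carry through to the guideline.

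**Working it through.** **Inputs from the protocol article (Sample size and sampling method).** Clusters: 13 + 14 = 27. Base size 240, design effect (DE) 1.5, final size 360. Units in the city: 82.

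**Assumptions not in the document.** Equal cluster sizes; the 1.5 applies to self-efficacy as well; and the intraclass correlation of each exposure (ICC_x), for which a range is shown.

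**Step 1, the plan's own figure.** 240 × 1.5 = 360. This reproduces exactly. The 240 is taken as given here, because its derivation does not affect this point.

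**Step 2, implied intraclass correlation.** Mean cluster size m = 360 / 27 = 13.33. From DE = 1 + (m − 1) × ICC, ICC = 0.5 / 12.33 = 0.041.

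**Step 3, means, proportions and exposures constant within a centre.** The ratio of naive to true standard error is 1/√1.5 = 0.816, so the naive one is 18% too small. The true level of a nominal 5% test is 2 × (1 − Φ(1.96/√1.5)) = 0.1095, about 11%. Coverage of a nominal 95% interval is 1 − 0.1095 = 0.890, about 89%.

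**Step 4, association tests on mother-level exposures.** Here DE = 1 + (m − 1) × ICC_x × ICC_y, with ICC_y = 0.041, and the true level is 2 × (1 − Φ(1.96/√DE)). The last column is a simulation of the unadjusted Pearson test (27 clusters, 360 mothers, 20,000 runs per row).

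| ICC_x (assumed) | DE | True SE / naive SE | Level, formula | Level, simulated |
|---|---|---|---|---|
| 0 | 1.00 | 1.00 | 0.050 | 0.048 |
| 0.04 | 1.02 | 1.01 | 0.052 | 0.050 |
| 0.2 | 1.10 | 1.05 | 0.062 | 0.059 |
| 0.5 | 1.25 | 1.12 | 0.080 | 0.082 |
| 1.0 (constant within centre) | 1.50 | 1.22 | 0.110 | 0.112 |

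**Step 5, sensitivity to the outcome's intraclass correlation.** Suppose self-efficacy had ICC_y of 0.01 to 0.02 (assumption). At ICC_x = 0.2 and ICC_y = 0.01, DE = 1 + 12.33 × 0.002 = 1.025 and the level is about 5.3%. At ICC_x = 0.5 and ICC_y = 0.02, DE = 1 + 12.33 × 0.01 = 1.123 and the level is about 6.4%.

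**Step 6, finite-population correction for means.** The sampled fraction of units is 27 / 82 = 0.33. Applying 1 − 0.33 = 0.67 to the between-cluster part gives DE = 0.041 × 13.33 × 0.67 + (1 − 0.041) ≈ 1.32. Naive coverage is then about 91% rather than 89%.

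**The case against.** The strongest reply concerns size. A reader might infer that every phase-two test has an 11% false-positive rate. The documents do not support that: the exposures in the Scales and data collection section (education, income, home ownership, social support, DASS-21) are measured on the mother or household, and no exposure is defined at centre level. Step 4 shows that a weakly clustered exposure leaves the test close to its nominal level. This stands.

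A reader might also suppose that socioeconomic variables vary mainly between neighbourhoods, so that those tests bear nearly the full effect. The article gives no intraclass correlation for any exposure, and all units lie in one city. The values 0.2 and 0.5 are illustrations.

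Two further limits stand. The 1.5 was applied to a size derived for psychological factors and depression, and carrying it to self-efficacy is an assumption. The analysis section names means and standard deviations but no confidence intervals, so under-coverage arises only if intervals or standard errors are reported. The 95% confidence coefficient in the sample-size section makes that plausible but not certain.

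It can also be said that a journal article leaves variance estimation to the full plan, and that the regression wording is too loose to pin down a model. This reduces the seriousness but does not answer the point. The article names specific tests, and those tests conflict with the sampling design and design effect that it also states.

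**Conclusion.** The inconsistency is real and its direction is clear: wherever exposure and outcome both cluster by centre, unadjusted tests reject too often. The size is modest for most of what this phase tests. If the design effect of 1.5 also describes self-efficacy, the true level is about 5% to 6% for exposures with an assumed ICC_x up to 0.2, and about 8% at an assumed 0.5. The figures of 18%, 89% and 11% belong only to standard errors or intervals for means and proportions and to any exposure constant within a centre. For means they shrink somewhat under a finite-population correction.

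This should be fixed, but the documents do not support the stronger conclusion that the phase-two associations would be unreliable without it. The phase is descriptive and analytical, and its results are one of several inputs to the expert panel.

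**What to change.** Retain the centre or post identifier in the data set and state one cluster-aware approach in the Data analysis section. The options are:

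- a mixed model with a random intercept for centre or post;
- regression with cluster-robust standard errors and a small-sample correction, since there are only 27 clusters;
- SPSS Complex Samples for means and bivariate comparisons, with centre versus post as the stratum and the 27 units as primary sampling units.

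Report the observed intraclass correlation for self-efficacy and the main exposures, so that readers can see whether the assumed 1.5 was borne out.

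No new data and no change to recruitment are needed. From the standard-error ratios above, intervals would widen by about 5% at ICC_x = 0.2, 12% at 0.5, and 22% for means without a finite-population correction. The remaining cost is a little more analysis work.

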### Third phase: integration of quantitative and qualitative data

To develop improvement strategies for increase ability of breastfeeding in mothers of premature infants, a comprehensive literature review will be carried out with a supportive approach to improve such practices. Following this, the results from qualitative and quantitative studies will be delivered to 10–12 experts. Then, their feedback and comments will be taken into account, using the nominal group technique.

## Discussion

The prevalence and duration of breastfeeding the premature infants tend to be lower than that of full-term infants [10], while feeding human milk to preterm infants may impact their long-term health and development [3, 5]. However, the mothers of premature infants face various problems in the process of breastfeeding due to different causes that can lead to its interruption and cause problems, which have repercussions on the health and well-being of the infants [10, 12, 16]. Very few studies have focused on these problems and psychosocial needs and opinions of mothers. Furthermore, listening to the mothers, and considering the affective factors on breastfeeding is a core need for quality family-centered care and can also help establish appropriate strategies. Therefore, the importance of breastfeeding and its affective factors should be recognized. It is also worth noting that there is no strategic guideline in Iran’s healthcare system for the improvement of breastfeeding in mothers of premature infants. The current study provides precise information about breastfeeding experiences, its related factors, barriers, and facilitators. The present research is the first one to investigate factors influencing breastfeeding which was performed using the mixed methods approach, and aimed to develop health practices improvement strategies. Data collection through qualitative and quantitative methods contributed to a better comprehension of the factors influencing breastfeeding. The mixed-methods approach focused on epistemological pluralism. As a result, this study made use of a combination of opinions, approaches, and different, even contradictory, methods to achieve a better understanding of the related concepts. The strategy proposed by this study may help healthcare professionals and policymakers to become aware of the factors influencing breastfeeding in mothers of premature infants, improve breastfeeding ability, and help to promote health in premature infants. Therefore, it is hoped that the strategy proposed in the current study leads to the improvement of breastfeeding practices in mothers of premature infants.

